### Assessment of the fluid status

For participants in the control group, clinical information obtained by physician physical examination is the standard of judgment. Clinical information is composed of four items, including measured BWT within 2 kg of the dry weight, BP less than 140/90 mmHg, absence of symptoms and signs for hypervolemia (dyspnea, edema, and crackle) or hypovolemia (dizziness and orthostatic hypotension).

For participants in the treatment group, the OH value measured by the Body Composition Monitor (BCM) (Fresenius, Medical Care Korea, Seoul, Korea), using an alternating current at 50 different frequencies (5–1000 kHz) combined with clinical information, represents the standard of judgment. The OH value is calculated using the BCM based on a physiologic tissue model that is composed of the individual’s normal ECW, normohydrated lean and adipose tissue. The OH value can be calculated from the difference between the normal expected ECW and the measured ECW
[9]. The BCM has been validated with isotope dilution methods against all available gold-standard methods in the healthy population and in patients on dialysis
[10–12].

### Physician’s practical treatment guidelines according to the volume status

The target BWT will be within 1 liter of the dry BWT. After randomization, participants in the control group will undergo BCM measurement at the beginning and end of the study. Both the physicians and participants will be blinded to the results. The physicians will prescribe PD solutions, drugs, and diet based on the clinical information that they obtain. Participants in the treatment group will undergo BCM measurement every 2 months over a 1-year period. Both the physicians and the participants will be notified of the results. Based on the BCM results combined with the clinical information, the physicians will prescribe PD solutions, diuretics, and diets. Figures 
2 and
3 show the management of hypervolemia and hypovolemia, respectively.

**Figure 2 Fig2:**
[figure not shown]
**Hypervolemia management flow chart.** APD, automated peritoneal dialysis; CAPD, continuous ambulatory peritoneal dialysis.

**Figure 3 Fig3:**
[figure not shown]
**Hypovolemia management flow chart.** APD, automated peritoneal dialysis; CAPD, continuous ambulatory peritoneal dialysis.

Participants who switch to HD or combined dialysis (PD with intermittent HD), receive kidney transplantation, transfer to other institutions, or die during the study will be dropped out of the study. Investigators or research coordinators will evaluate treatment adherence and give scores for each particular item, including 1) percentage of self-reported medical records >80%, 2) percentage receiving PD solutions >80%, 3) adherence to examinations including complete blood count (CBC), chemistry, peritoneal equilibrium test, Kt/V (where K is dialyzer clearance of urea, t is dialysis time, and V is volume of distribution of urea, approximately equal to the patient's total body water), and 4) adherence to the scheduled visits.

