### Outcome measures

The primary outcome is the change in GFR between months 0 and 12 after starting treatment. The secondary outcomes will include GFR measured by urine collection, calculated by the mean of the Cr and urea clearance at month 12; time to the anuric state (urine volume <100 ml/day); and fatal and nonfatal cardiovascular events, including acute myocardial infarction, stroke, unstable angina, and cardiovascular revascularization. Parameters obtained by echocardiographic measurements, such as the left ventricular mass index, E/e′ ratio, left ventricular end-diastolic pressure, left ventricular ejection fraction, left atrial volume index, and BP at month 12; parameters measured by BIS, such as the OH value, ECW, and ECW/ICW; hospitalization, cardiovascular and all-cause mortality, and transfer to HD over the course of 1 year; pulse wave velocity (PWV), type and number of PD fluid and diuretics at month 12, and laboratory findings including high-sensitivity C-reactive protein (hs-CRP), N-terminal prohormone of brain natriuretic peptide, and cardiac troponin T, will also be evaluated as tertiary outcomes.

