**Table 1 Tab1:** **Data collection schedule of the COMPASS study**

Parameter	Visit time (months)							
	-1	0	2	4	6	8	10	12
Demographic information	X							
Charlson Comorbidity Index	X							
Physical examination^1^	X	X	X	X	X	X	X	X
Medication review^2^	X	X	X	X	X	X	X	X
Routine laboratory data^3^		X	X	X	X	X	X	X
Special laboratory data^4^		X						X
RRF, urine volume		X						X
Compliance		X	X	X	X	X	X	X
New events^5^		X	X	X	X	X	X	X
BCM measurement								
Treatment group		X	X	X	X	X	X	X
Control group		X						X
Kt/V		X						X
Peritoneal equilibration test		X						
PWV		X						X
Echocardiography		X						X
PD solution, medication change		X	X	X	X	X	X	X

BCM*,* Body composition monitoring; COMPASS*,* Control Of fluid balance guided by body composition Monitoring in patients on PeritoneAl dialySiS trial; Kt/V*,* Calculated using single pool equation; PD*,* Peritoneal dialysis; PWV*,* Pulse wave velocity; RRF*,* Residual renal function.

^1^Includes body weight with an empty abdomen, blood pressure, pulse rate, and edema.

^2^Number of anti-hypertensive medications and diuretics and the type of PD solution.

^3^Complete blood count, electrolyte, serum creatinine, protein, albumin, calcium, phosphorous, and fasting glucose.

^4^Total cholesterol, triglyceride, low-density lipoprotein cholesterol, high-sensitivity C-reactive protein, hemoglobin A1C, intact parathyroid hormone, N-terminal prohormone of brain natriuretic peptide, and cardiac troponin T.

^5^Any new clinical event, including hospitalization and peritonitis, will be recorded during the study period.

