### Statistical analyses

The statistical analyses will be conducted both on a per-protocol (PP) and an intention-to treat (ITT) basis. For PP analysis, all participants who complete the study will be included to evaluate the primary and secondary outcomes. For the ITT analysis, all participants who are enrolled and randomized to one of the two groups and who complete the first visit will be included.

Basic statistics will be reported in terms of mean ± SD for continuous variables, or as percentages for categorical variables. Differences between groups will be analyzed using Student’s *t*-test for continuous variables and the *χ*^2^ test or Fisher’s exact test for categorical variables. The difference in GFR between month 0 and month 12 will be compared between the two groups using Student’s *t*-test for the primary outcome. Analysis of covariance (ANCOVA) will be used to analyze the primary outcome as the secondary analysis to adjust the baseline value. Multivariate Cox proportional hazard regression models will be used to analyze the time to development of anuria. Although the institutions are mainly located in large cities, thereby limiting the likelihood of any important cluster effect, we will be sure to accommodate possible clustering in our models and analysis as required. A value of *P* < 0.05 will be considered statistically significant. All analyses will be performed using SPSS Statistics software (v21.0; IBM Corporation, Armonk, NY, USA).

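### Participants who leave PD, transfer or die are dropped from the study, so they have no post-baseline GFR and later events promised over one year are lost; bias is plausible, but its direction is not established

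*Protocol article*

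**What the plan says.** The rule stands at the end of the section on the physician's practical treatment guidelines, after Figure 3. It opens with "Participants who switch to HD or combined dialysis (PD with intermittent HD" and continues "receive kidney transplantation, transfer to other institutions, or die during the study will be dropped out of the study". The article describes no follow-up after that point.

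The outcomes and analysis sets that the rule touches are:

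- **Primary outcome** (Outcome measures): "The primary outcome is the change in GFR between months 0 and 12 after starting treatment". It is compared by Student's t-test, with ANCOVA as a secondary analysis (Statistical analyses).
- **Secondary outcomes** include time to anuria and "fatal and nonfatal cardiovascular events, including acute myocardial infarction, stroke, unstable angina, and cardiovascular revascularization".
- **Tertiary outcomes** include "hospitalization, cardiovascular and all-cause mortality, and transfer to HD over the course of 1 year".
- **Schedule** (Table 1): the row "RRF, urine volume" is marked at months 0 and 12 only. New events are recorded at every visit from month 0 to month 12.
- **PP set**: "For PP analysis, all participants who complete the study will be included to evaluate the primary and secondary outcomes".
- **ITT set**: "all participants who are enrolled and randomized to one of the two groups and who complete the first visit will be included".

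**The concern.** The rule treats the end of PD, or of care at a study hospital, as the end of study participation. This has two consequences.

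First, GFR is measured once after baseline, at month 12. Anyone who leaves earlier contributes no GFR change. The ITT set keeps them by name, but a t-test on change cannot use them unless a value is imputed. As designed, the ITT comparison of the primary outcome moves towards the completers-only PP comparison.

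Second, whatever happens after a switch to HD, a transplant or a transfer goes unrecorded, although mortality and hospitalization are to be assessed over the full year.

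Losing these participants need not be random. HD transfer and death are themselves listed outcomes. The Background links overhydration to mortality and volume depletion to faster loss of residual function, and the hypothesis is that the intervention affects residual function. The trial is open-label, so a change of modality is decided with the arm known. Exit can therefore depend on both arm and residual function, and the participants with a month-12 GFR would then be a selected group.

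**Working it through.** **1. The plan's sample size.** Inputs from Sample size calculations: GFR changes of -16.8 ± 19.9 and 0.09 ± 40.9 l/week/1.73 m², two-sided α = 5%, power 80%, drop-out 20%.

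- Difference: 0.09 - (-16.8) = 16.89.
- Pooled SD: √[(19.9² + 40.9²)/2] = 32.16.
- n per group: 2 × [32.16 × (1.960 + 0.842)/16.89]² = 56.9, rounded up to 57.
- With drop-out: 57 × 1.20 = 68.4, rounded up to 69. This reproduces the stated figure.

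**2. Power is not the main issue.** If 20% have no month-12 GFR, 69 × 0.80 = 55.2 per group remain and power is 78.8% (normal approximation). With all 69 measured it is 87.0%. The question is bias.

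**3. What the documents allow one to say about bias.** Let p be the share missing in an arm, and g the amount by which the mean GFR change of leavers is worse than that of completers. Then

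completers' difference - full difference = p(BIS) × g(BIS) - p(control) × g(control).

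The article gives neither p nor g for these exits. Its 20% is attributed to poor compliance, not to HD transfer, transplant, transfer or death. Assumed values show the range:

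- 20% missing in each arm, same g: bias 0.
- 25% control and 15% BIS, g = 10 to 30: -1.0 to -3.0, which is 6% to 18% of 16.89.
- 30% control and 10% BIS, g = 10 to 30: -2.0 to -6.0, which is 12% to 36%.
- 20% in each arm, with g of 30 in one arm and 10 in the other: 0.2 × (30 - 10) = 4.0, which is 24%, in either direction.

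**4. A selection rule applied to the plan's own means.** Assume normal changes, and that everyone in either arm below a cut-off c leaves. Set c so that it removes the worst 5%, 10% or 15% of controls: c = -16.8 + SD(control) × z, with z = -1.645, -1.282 or -1.036. The completers' mean in an arm with mean m and SD s is m + s × φ(a)/[1 - Φ(a)], where a = (c - m)/s.

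Example with the plan's own SDs at 5%: c = -16.8 - 1.645 × 19.9 = -49.5. The completers' means are -14.64 (control) and 8.90 (BIS), so the difference is 23.5.

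| SDs (control, BIS) | Controls lost | BIS lost | Completers' difference | Change from 16.89 |
|---|---|---|---|---|
| 32.16, 32.16 | 5% | 1.5% | 14.6 | -13% |
| 32.16, 32.16 | 10% | 3.5% | 13.2 | -22% |
| 32.16, 32.16 | 15% | 5.9% | 12.1 | -28% |
| 19.9, 40.9 | 5% | 11% | 23.5 | +39% |
| 19.9, 40.9 | 10% | 15% | 24.2 | +43% |
| 19.9, 40.9 | 15% | 18% | 24.5 | +45% |

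The sign changes because the larger SD in the BIS arm puts more of that arm below the cut-off at 5% and 10% (and still 18% against 15% at the highest), and its lost values lie further out.

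**5. Which events are lost.**

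| Exit | The exit event | Events afterwards |
|---|---|---|
| Switch to HD or combined dialysis | Transfer to HD is an outcome; can be counted | Lost |
| Transplant | Can be recorded | Lost |
| Transfer to another institution | Not a listed outcome | Lost |
| Death | Is an outcome; can be counted | None possible |

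**The case against.** Several stronger readings are tempting, and the documents do not support them.

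- **The ITT analysis is impossible.** An ITT set is defined. Analysing it needs a method for missing values, which an article commonly leaves to the SAP or full protocol, and neither is shown. That gap is no finding. What stands is that no SAP can recover data that the protocol chose not to collect.
- **The effect is attenuated because the worst controls disappear.** This holds under the pooled SD and reverses under the SDs that the article gives. Neither direction can be claimed.
- **Deaths and HD transfers go uncounted.** The event that causes the exit can still be recorded, since new events are noted at each visit. Only what follows is lost, and nothing can follow death.
- **Cardiovascular follow-up contradicts the outcome definition.** The abstract confines cardiovascular events to the treatment period, so ending their collection at exit is arguably consistent with it. The conflict is clear only for the tertiary outcomes planned over one year.
- **Early leavers are treated as event-free in a χ² test.** The article names χ² or Fisher tests for categorical variables in general and does not say how leavers are coded.
- **Every exit reason is tied to residual function.** Nothing links institutional transfer to it. There the problem is avoidable loss to follow-up.

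It is also fair that patients likely to stop PD or be transplanted within a year are excluded at entry, which should make these exits less common. How many will occur is unknown.

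**Conclusion.** The point holds in a limited form. The drop-out rule and the two-point GFR schedule together leave participants who exit early without any post-baseline GFR. They also cut off later deaths and hospitalizations that the plan assesses over one year. This follows from the stated text and does not depend on an SAP.

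That the primary comparison is biased as a result is plausible, not shown. It rests on the assumption that leaving is related to GFR change and differs between arms. The illustrations run from no bias, through 28% attenuation, to 45% inflation, depending on assumptions that the article cannot settle. None of these figures is an estimate of the bias in this trial. The loss of power at 20% missing is small.

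The change is worth making because the lost data cannot be recovered later, the primary endpoint is involved, and the article reports that recruitment is still under way.

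**What to change.** - Reword the rule so that these participants stop the study intervention but remain in follow-up to month 12.
- For those leaving PD or transferring, bring the month-12 urine collection forward to the exit visit where possible.
- Obtain vital status, cardiovascular events and hospitalization to month 12 from records or by phone for all participants.
- Analyse the primary outcome in the ITT set using the exit values, with a sensitivity analysis for HD transfer and death.

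Cost: a change of protocol wording, one collection moved rather than added for leavers, a record or phone check at month 12, and some extra analysis. Exit GFR values will be taken at varying times before month 12, so they are not equivalent to month-12 values, and the analysis must allow for this. No change to dialysis or other clinical management is proposed.

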### Clinical and laboratory evaluations

Physical examination, medication reviews including PD solutions, fluid balance evaluation (semi-quantitative scale),. and laboratory evaluations, including CBC, electrolytes, Cr, protein, albumin, calcium, phosphorous, and fasting glucose will be conducted every 2 months.

Laboratory evaluations, including total cholesterol, triglyceride, low-density lipoprotein cholesterol, hs-CRP, hemoglobin A1C, intact parathyroid hormone, N-terminal prohormone of brain natriuretic peptide, cardiac troponin T, and weekly Kt/V_urea_, will be performed at months 0 and 12 of treatment. Echocardiography will be performed, and PWV will be measured using a Colin pulse waveform analyzer (Colin CO, Ltd, Komaki, Japan) at months 0 and 12 after treatment. The study schedule is shown in Table 
1.

**Table 1 Tab1:** **Data collection schedule of the COMPASS study**

Parameter	Visit time (months)							
	-1	0	2	4	6	8	10	12
Demographic information	X							
Charlson Comorbidity Index	X							
Physical examination^1^	X	X	X	X	X	X	X	X
Medication review^2^	X	X	X	X	X	X	X	X
Routine laboratory data^3^		X	X	X	X	X	X	X
Special laboratory data^4^		X						X
RRF, urine volume		X						X
Compliance		X	X	X	X	X	X	X
New events^5^		X	X	X	X	X	X	X
BCM measurement								
Treatment group		X	X	X	X	X	X	X
Control group		X						X
Kt/V		X						X
Peritoneal equilibration test		X						
PWV		X						X
Echocardiography		X						X
PD solution, medication change		X	X	X	X	X	X	X

BCM*,* Body composition monitoring; COMPASS*,* Control Of fluid balance guided by body composition Monitoring in patients on PeritoneAl dialySiS trial; Kt/V*,* Calculated using single pool equation; PD*,* Peritoneal dialysis; PWV*,* Pulse wave velocity; RRF*,* Residual renal function.

^1^Includes body weight with an empty abdomen, blood pressure, pulse rate, and edema.

^2^Number of anti-hypertensive medications and diuretics and the type of PD solution.

^3^Complete blood count, electrolyte, serum creatinine, protein, albumin, calcium, phosphorous, and fasting glucose.

^4^Total cholesterol, triglyceride, low-density lipoprotein cholesterol, high-sensitivity C-reactive protein, hemoglobin A1C, intact parathyroid hormone, N-terminal prohormone of brain natriuretic peptide, and cardiac troponin T.

^5^Any new clinical event, including hospitalization and peritonitis, will be recorded during the study period.

### Safety issues

The BIS method approved by the US Food and Drug Administration has been used in clinical practice, particularly in Europe. Weak alternating currents into the body are known to be not harmful.

### Sample size calculations

No previous report has evaluated the effect of BIS-guided fluid management on RRF in patients on PD. We therefore referred to a study showing that GFR changes over 1 year in a conventional PD solution treatment group and in a biocompatible PD solution treatment group were -16.8 ± 19.9 and 0.09 ± 40.9 l/week/1.73 m^2^, respectively
[13]. We adjusted the sample size for an estimated drop-out rate of 20% due to poor compliance, a two-sided level of significance of α = 5%, and a power of 80%, and found that 69 participants will be required in each group to find a significant difference using Student’s *t*-test. A total of 138 participants will be included in the analysis.

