### Randomization

The randomization process will be conducted using a web-based computer program. A list of random numbers will be generated by a computerized random allocation system operated by the Medical Statistics Support Team in Seoul National University Hospital. Eligible participants will be randomly assigned 1:1 to either the control group (fluid management based on the clinical information alone) or treatment group (BIS-guided fluid management along with clinical information). Randomization will be stratified based on the institution and presence of diabetes mellitus, and will utilize a randomized block design.

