[23–25]. Although some studies have suggested cutoff thresholds for the definition of the OH in patients on HD and patients on PD of 2.5 and 2.0 liters, respectively
[19, 26, 27], we consider an ECW within ±1.1 liter as normal hydration.

There is a chance that patients within the same institution will be more correlated than patients between institutions. To avoid this, we will investigate for possible clustering of patients at the recruitment institution level, and will accommodate such clustering in our models and analysis as required. We also conservatively calculate the sample size, assuming a high drop-out rate, to overcome this potential problem.

A limitation of this study is that we will include both prevalent and incident patients on PD. Although a study targeting only incident patients on PD might provide more solid results, we will adjust the dialysis vintage in the multivariable analyses.

In summary, the COMPASS study is the first prospective, randomized controlled trial to evaluate the clinical usefulness of BIS-guided fluid management in patients on PD. The aim of this study is to evaluate whether BIS-guided fluid management has a beneficial effect on the decline of RRF, cardiac parameters, and cardiovascular outcomes.

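### The stated inputs with 20% drop-out need 72 to 73 participants per group, not 69, and 138 is given as both the number enrolled and the number analysed (minor)

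*Protocol article*

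**What the plan says.** All the planning inputs are in the Protocol article.

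- **Effect and spread** (Sample size calculations): one-year GFR changes in the two arms of a borrowed PD-solution study "were -16.8 ± 19.9 and 0.09 ± 40.9 l/week/1.73 m^2^, respectively".
- **Error rates** (same section): "a two-sided level of significance of α = 5%, and a power of 80" per cent.
- **Drop-out** (same section): "We adjusted the sample size for an estimated drop-out rate of 20% due to poor compliance".
- **Result** (same section): "and found that 69 participants will be required in each group to find a significant difference", followed by "A total of 138 participants will be included in the analysis".
- **Allocation** (Randomization): "Eligible participants will be randomly assigned 1:1 to either the control group" or the treatment group.
- **Primary test** (Statistical analyses): "The difference in GFR between month 0 and month 12 will be compared between the two groups using Student’s" t-test.

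The Abstract, under Methods/design, gives the same 138 as the number to be enrolled and randomised. Table 1 schedules residual renal function and urine volume at months 0 and 12 only. The section on physicians' treatment guidelines says that participants who move to HD or combined dialysis, are transplanted, transfer to another institution or die leave the study. Statistical analyses defines the PP set as completers and the ITT set as everyone randomised who completes the first visit.

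**The concern.** Two things do not fit together.

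First, a number that has been adjusted for 20% drop-out should still leave the evaluable number that the power calculation needs once 20% are gone. Taking 20% off 69 leaves about 55 per group, and the stated inputs need more than that.

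Second, 138 has two roles. It is the enrolment target, which already contains the drop-out allowance, and it is also the number said to be analysed. For a month 0 to month 12 change, participants who leave early have no scheduled second measurement, so both cannot be true of the observed primary outcome.

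What is at stake is the accuracy of the stated design: the enrolment figure, the number contributing to the primary test and the 80% power do not agree. Someone reading the final result against this plan could not tell which power applies.

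**Working it through.** **Inputs** (sources as listed above)

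- Difference: 0.09 − (−16.8) = 16.89 l/week/1.73 m²
- SDs: 19.9 and 40.9. The sum of variances is 396.01 + 1672.81 = 2068.82, and the root-mean-square SD is √(2068.82/2) = 32.16
- Standardised effect: 16.89/32.16 = 0.525
- Two-sided α = 0.05 (z = 1.960); power 80% (z = 0.842); allocation 1:1; drop-out 20%

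**Step 1: evaluable number per group**

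Normal approximation: n = (1.960 + 0.842)² × (19.9² + 40.9²) / 16.89² = 7.849 × 2068.82 / 285.27 = 56.9, so 57.

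Student's t-test (noncentral t): n = 57.9, so 58. Power is 79.4% at 57 and 80.1% at 58.

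**Step 2: reproduce the stated 69**

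57 × 1.2 = 68.4, which rounds up to 69, the plan's figure.

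**Step 3: the inflation that 20% drop-out requires**

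If a fraction d is lost, the number to randomise is n/(1 − d).

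| Basis | Evaluable per group | Divided by 0.8 | Per group | Total |
|---|---|---|---|---|
| Normal | 57 | 71.25 | 72 | 144 |
| Student's t | 58 | 72.5 | 73 | 146 |

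The shortfall against the plan is 3 to 4 per group, or 6 to 8 in total.

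**Step 4: does another choice of method give 69 with division by 0.8?**

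| Variant | Evaluable per group | Per group after dividing by 0.8 |
|---|---|---|
| Welch t-test | 59 | 74 |
| One-sided 5% | 45 | 57 |
| Arithmetic mean of the two SDs | 51 | 64 |
| Larger SD only | 93 | 117 |
| Smaller SD only | 22 | 28 |

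None gives 69.

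**Step 5: what 69 per group delivers**

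69 × 0.8 = 55.2, so about 55 per group and 2 × 55.2 ≈ 110 in total.

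Normal power at 55: 16.89/√(2068.82/55) = 2.754; 2.754 − 1.960 = 0.794; Φ(0.794) = 78.6%. By Student's t it is 77.9%, and by Welch 77.6%.

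If all 69 per group did have a month-12 value, power would be 86.5% (t) or 87.0% (normal). The two roles given to 138 therefore correspond to about 78% and about 87% power. Neither is the stated 80%.

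**The case against.** **The cause is inferred.** The article gives no inflation formula. Multiplying by 1.2 reproduces 69 only from the normal-approximation 57. From the t-based 58 it gives 69.6, so 70, although the section names Student's t-test. This stands: the route is a plausible explanation and not a documented one. The shortfall does not depend on it, because 69 less 20% is about 55 whichever way 69 was reached.

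**The effect is small.** On the method that yields 57, the loss of power is 1.4 points; on the t-test it is 2.1. The 69 per group would suffice if losses stayed at 17.4% (12/69, leaving 57) or 15.9% (11/69, leaving 58). The effect and SDs are also borrowed from a different intervention, so two points of power lie well within the uncertainty of the planning. This stands, and it sets the grade.

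**The ITT set could nominally hold nearly all 138.** This is true of its definition, and the handling of missing values may properly be left to a document not shown. It does not supply month-12 measurements that Table 1 does not schedule for people who have left. The sentence about the analysis is still wrong for observed primary outcomes.

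**Stronger readings that a reader might draw.** One is that departures through HD, transplant, transfer or death come on top of the 20%, because that figure is attributed to poor compliance. No passage says so. The article uses the idea of dropping out in both places, and the 20% may well be meant to cover everything. For the same reason, power at higher loss rates would rest on rates that the article does not give. Another is that the Discussion is wrong to say "We also conservatively calculate the sample size, assuming a high drop-out rate, to overcome this potential problem". Whether 20% is a high rate is a judgement about expected losses, and a slip in applying the rate does not refute it.

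**Conclusion.** The point holds as a minor arithmetic and wording error. On the article's own inputs, 80% power after 20% drop-out needs 72 to 73 per group (144 to 146 in total). The planned 69 per group leaves about 55, with power of 77.9% (t) or 78.6% (normal). In addition, 138 cannot be both the enrolled number that carries a drop-out allowance and the number with an observed month 0 to month 12 change; the latter is about 110.

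This assumes that the planning difference and SDs are taken at face value, that losses are 20% and equal in the two groups, and that a participant who drops out has no month-12 GFR. The relation between the 20% and the listed reasons for leaving is an ambiguity to clear up, and the documents do not establish it as an extra loss. Nothing here suggests that the trial is materially underpowered for its own planning effect.

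**What to change.** Either of two corrections restores agreement in Sample size calculations.

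1. **Keep 138.** Say that it is the number randomised, and state that about 110 (55 per group) are expected to be evaluable for the primary outcome, with power of about 78% by Student's t-test.
2. **Keep 80% power.** Say that 57 to 58 evaluable participants per group are needed, and that with 20% drop-out this means randomising 72 to 73 per group (144 to 146). The Abstract must then change to match.

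In either case, replace the statement that 138 will be analysed, and say that the 20% covers all reasons for a missing month-12 GFR, not poor compliance alone.

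The first option costs only text and a slightly less favourable stated power. The second costs 6 to 8 more participants. As recruitment is already under way, the first is the simpler choice.
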